### Schedule of Events and Timeline

| Study Activity                                    | Screening
(within 1
week
admission) | Baseline
(within 72
hrs. prior to
treatment 1) | Treatment
Visits | Post-
treatment
(within 72
hrs. after
treatment 10) |
|---------------------------------------------------|----------------------------------------------|---------------------------------------------------------|---------------------|-----------------------------------------------------------------|
|                                                   | Visit 0                                      | Visit 1
(tDCS #1 is
same as Visit
1)           | Visits 1-10         | (tDCS #10 is
same as Visit
10)                            |
| Informed Consent                                  |                                              | X                                                       |                     |                                                                 |
| Medical History                                   | X                                            |                                                         |                     |                                                                 |
| Medication History                                | X                                            |                                                         |                     |                                                                 |
| Pregnancy Test (from EMR)                         | X                                            |                                                         |                     |                                                                 |
| Physical Exam                                     |                                              | X                                                       |                     |                                                                 |
| EEG                                               |                                              | X                                                       |                     | X                                                               |
| fNIRS (NIRSIT)                                    |                                              | X                                                       |                     | X                                                               |
| tDCS (2 mA, 30 min)                               |                                              |                                                         | X                   |                                                                 |
| PHQ-9 (from EMR)                                  | X                                            |                                                         |                     |                                                                 |
| MADRS                                             |                                              | X                                                       |                     | X                                                               |
| Cognitive assessments (Stroop, HVLT-R, DSCT)      |                                              | X                                                       |                     | X                                                               |
| Other Assessments (ACE, premorbid IQ, SES, WRART) |                                              | X                                                       |                     |                                                                 |
| Device Interrogation Save to Disk                 |                                              |                                                         |                     |                                                                 |
| Concurrent Medications                            |                                              | X                                                       |                     |                                                                 |
| Adverse Events                                    |                                              |                                                         | X                   | X                                                               |
| Serious Adverse Events                            |                                              |                                                         | X                   | X                                                               |

### Timeline

[figure not shown]

## 7 Statistical Plan

### 7.1 Sample Size Determination

Because this is a feasibility pilot study, formal power calculations are not needed. Target accrual is 10 subjects.

### 7.2 Statistical Methods

#### Descriptive Statistics

Baseline values for demographic, clinical, and outcome variables (primary and secondary) will be reported with descriptive statistics.

#### Handling of Missing Data

In the event where missing data cannot be prevented, we will include cases with complete data for specific analyses. In the study report, we will be transparent about the extent of missing data and the methods used to handle it to help convey the limitations of the study.

#### Multiplicity

Because this is a pilot study aimed at generating hypotheses, no adjustment for multiple comparisons will be made.

#### Primary Hypothesis:

**Hypothesis 2.1:** We hypothesize that the proposed 5-day tDCS treatment protocol will be feasible (enrollment of 70% of eligible patients), acceptable (80% of study participants completing 80% of the 10-session tDCS treatments) and tolerable (overall tolerability rating of "very tolerable" by self-report) to implement in the inpatient psychiatric setting.

Percentage of subjects completing the study and adhering to the protocol will be reported.

### **Secondary Hypothesis:**

**Hypothesis 2.2.1.a:** We hypothesize that patients treated with the 5-day tDCS treatment protocol will have a decrease in mean MADRS scores post-tDCS.

**Hypothesis 2.2.1.b:** We hypothesize that patients treated with the 5-day tDCS treatment protocol will demonstrate changes in cognitive measures (Stroop Test, HVLT-R, and DSCT) post-tDCS.

T-tests or Wilcoxon signed rank tests will be used to compare pre- and post-tDCS measures on depression rating scales (MADRS, SHAPS) and cognition (Stroop, HVLT-R, DSCT). The effect sizes reported will include the proportion that improved, and both raw mean and standardized mean differences, i.e., Cohen's d.

**Hypotheses 2.2.2.a:** We hypothesize that the baseline PAF will have an indirect correlation with baseline MADRS scores in depressed patients.

**Hypothesis 2.2.2.b:** We hypothesize that there will be an increase in mean PAF scores after the 5-day tDCS treatment protocol.

Pearson or Spearman correlation will be used to estimate the correlation between MADRS scores and PAF at baseline. T-tests or Wilcoxon signed rank tests will be used to compare pre- and post-tDCS PAF scores. The effect sizes reported will include the correlation coefficient, proportion that improved, and both raw mean and standardized mean differences, i.e., Cohen's d. Treatment response will be defined as 50% or more improvement in MADRS score at post-treatment from pre-treatment. In the context of exploratory analysis, logistic regression will be used to assess associations between treatment response with each baseline characteristic.

**Hypothesis 2.2.2c:** We hypothesize that baseline characteristics (*ACE, pIQ, WRART, SES*) *will be predictive of treatment response.*

Pearson or Spearman correlation will be used to estimate the correlation between MADRS scores and PAF at baseline. T-tests or Wilcoxon signed rank tests will be used to compare pre- and post-treatment PAF scores. Treatment response will be defined as 50% or more improvement in MADRS score at post-treatment from pre-treatment. Logistic regression will be used to assess associations between treatment response with each baseline characteristic.

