## **Efficacy of tDCS on Depression**

In a systematic review of tDCS for the treatment of depression, treatment parameters used across studies included ranges of 1-2 mA current intensity, 25-35 cm^2 electrode size, F3 (anodal) electrode position, right supraorbital (cathodal) reference electrode position, 20-30 minutes once or twice per day treatments, with a total of 5-15 stimulations over 1-3 weeks treatment duration. [7] Results of tDCS studies show inconsistent efficacy due to small sample sizes and heterogeneity of study populations. A recent meta-analysis showed modest effect of tDCS compared to sham ((k=25, Hedges'sg= 0.46, 95% confidence interval [CI]: 0.22–0.70) in treating depressive episodes. [8]

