### **4.4 Early Withdrawal of Subjects**

#### **4.4.1 When and How to Withdraw Subjects**

Subjects will be withdrawn from the study prior to completing study procedures in the following circumstances:

- Subject decision to withdraw from the study (withdrawal of consent)
- Subject inability to adhere to protocol requirements
- Severe adverse effects (SAEs) requiring medical intervention
- If the investigators determine it is in the best interest of the subject

There are no anticipated risks particular to early or abrupt discontinuation of tDCS. If subjects discontinue tDCS treatments or withdraw early and require ongoing medical treatment, appropriate referrals will be arranged. Should a subject experience any medical emergency during participation in a study visit, whether related to the study or not, the subject will be evaluated by clinical on-call inpatient psychiatric staff.

If an enrolled subject withdraws from the study prior to completion, an attempt will be made to enroll another subject in order to achieve the target enrollment.

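### Section 7.2 names Cohen's d for about 10 subjects with no small-sample correction: expected magnitude is about 9% too large at n = 10 and 13% at n = 8 if the SD has n − 1 df

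*Protocol*

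**What the plan says.** Under the secondary hypotheses in Section 7.2, the protocol names its effect sizes in two places. For MADRS, SHAPS and the cognitive tests: "The effect sizes reported will include the proportion that improved", followed by "both raw mean and standardized mean differences, i.e., Cohen's d". For peak alpha frequency (PAF): "The effect sizes reported will include the correlation coefficient, proportion that improved", followed by the same phrase ending in Cohen's d. Neither place says which SD is the denominator or mentions a small-sample correction.

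The number of pairs is set by several sections:
- Section 7.1: "Target accrual is 10 subjects", with the remark that "formal power calculations are not needed".
- Section 7.2, missing data: "we will include cases with complete data for specific analyses".
- Section 4.4.1, on withdrawals: "an attempt will be made to enroll another subject in order to achieve the target enrollment".
- Section 4.4.2 keeps data from withdrawn subjects and invites those who stop treatment to the post-treatment assessments.
- Section 7.3 analyses all treated subjects, with a sensitivity set of those who completed at least 80% of sessions.

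Sections 2.2 and 3.3 class these endpoints as exploratory, and the multiplicity paragraph of Section 7.2 describes the pilot as hypothesis-generating.

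**The concern.** Cohen's d divides a mean by a sample SD. In small samples the reciprocal of a sample SD is too large on average, so the expected value of d lies further from zero than the true standardized effect. The excess is negligible in a large trial but not at 10 pairs or fewer. The protocol names this statistic as the standardized summary for all pre-post outcomes in Section 7.2, and a known multiplier removes the bias.

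What is at stake is limited: the standardized estimates this pilot passes on would be somewhat too large in magnitude, by an amount that depends on a denominator the text leaves open.

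**Working it through.** The protocol states no power, SD or expected d, so there is no figure of its own to reproduce.

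**Inputs.** Target n = 10 (Section 7.1). Complete-case analysis can lower the number of pairs; n = 8 serves as the lower case, matching the 80% completion threshold (0.80 × 10 = 8). Replacement of withdrawn subjects can raise the number above 10. Assumed, because the documents do not give them: normal data, a pre-post correlation r from 0 to 0.7, and an illustrative true effect of 0.46.

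**Step 1. Denominator on n − 1 df (SD of change or baseline SD).** With m = n − 1, J(m) = Γ(m/2) / [√(m/2) · Γ((m − 1)/2)], and the expected d is the true effect divided by J. Relative excess = 1/J − 1.

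| Pairs n | df m | J | Excess of expected d |
|---|---|---|---|
| 12 | 11 | 0.930 | 7.5% |
| 11 | 10 | 0.923 | 8.4% |
| 10 | 9 | 0.914 | 9.4% |
| 9 | 8 | 0.903 | 10.8% |
| 8 | 7 | 0.888 | 12.6% |
| 7 | 6 | 0.869 | 15.1% |

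The approximation 1 − 3/(4m − 1) gives 0.9143 at m = 9 and 0.8889 at m = 7. Simulation of paired normal data (300,000 replicates per setting) gave 9.2 to 9.6% at n = 10 and 12.4 to 12.8% at n = 8 for these two denominators.

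**Step 2. Denominator is the average pre/post SD** (square root of the mean of the two variances). Two correlated variances carry more than n − 1 df, so the bias is smaller. Simulated excess:
- n = 10: 4.5%, 4.5%, 5.5% and 6.5% at r = 0, 0.3, 0.5 and 0.7.
- n = 8: 5.9%, 6.4%, 7.0% and 8.3% at the same correlations.

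Using J on 2n − 2 df gives 4.4% at n = 10 and 5.8% at n = 8, which agrees with r = 0 but is too small a correction when r is high.

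**Step 3. Size against sampling error.** Take a true effect of 0.46 on the SD of change (the r = 0.5 simulation).
- n = 10: 0.46 / 0.9139 = 0.503, an excess of 0.043. The simulated sampling SD of d is 0.384, and 0.043 / 0.384 = 0.11.
- n = 8: 0.46 / 0.8882 = 0.518, an excess of 0.058. The sampling SD is 0.451, and 0.058 / 0.451 = 0.13.

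**Step 4. Effect of correcting.** The reduction in the reported value is 1 − J on n − 1 df: 1 − 0.914 = 8.6% at n = 10 and 1 − 0.888 = 11.2% at n = 8. With the average SD at n = 10 it is 1 − 1/1.045 = 4.3% to 1 − 1/1.065 = 6.1%.

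**The case against.** The strongest reply is that the protocol never says uncorrected. It gives a name, and the denominator, correction and interval are details that a statistical analysis plan may settle. That stands in part: the missing denominator is not an error in itself. But the name is conventionally used for the uncorrected statistic and it appears twice, so an analysis plan that follows the protocol literally would report it. The point is an improvement to something the protocol names, not a complaint about silence.

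A second reply is that the bias cannot change any conclusion of this pilot. This also stands. It is about one-ninth to one-eighth of the sampling SD, the endpoints are exploratory, and an uncontrolled change with medication adjustments allowed (Section 5.5) carries larger uncertainties that J does not address. This limits the point to a minor one.

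Four stronger readings are tempting, and the documents do not support them:
- **A mismatch with a Hedges' g benchmark.** Section 1.1 reports "A recent meta-analysis showed modest effect of tDCS compared to sham ((k=25, Hedges'sg= 0.46, 95% confidence interval [CI]: 0.22–0.70", but only as background. The protocol never uses it as a target or comparator. It is an active-versus-sham contrast, so applying J to a single-arm change would not make the two comparable.
- **Overstatement of every effect.** The bias is an expectation, not a property of each estimate, and only the standardized measure has it. Raw differences and the proportion improved are reported alongside.
- **Bias in the favourable direction.** It is away from zero, so a worsening would be exaggerated too. Hypothesis 2.2.1b predicts change in cognition without a direction.
- **An undersized next trial.** Required n varies as 1/d², so one could compute 1 − 1/1.094² = 16% to 1 − 1/1.126² = 21%. No section says that a later trial will be sized on this d, and the raw mean difference would be available for planning.

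Nor is a ceiling of 10 pairs guaranteed. Replacement could give 11 or 12, where the excess on n − 1 df is 8.4% or 7.5%.

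**Conclusion.** The point holds as a minor improvement. With about 10 subjects, Cohen's d without a small-sample correction has an expected magnitude too large by about 9% at n = 10 and 13% at n = 8 when the denominator has n − 1 df. With the average pre/post SD the excess at n = 10 is about 4.5 to 6.5%. It exceeds 13% on n − 1 df only if complete pairs fall below 8. The figures rest on normal data; those for the average SD also rest on a pre-post correlation between 0 and 0.7 and equal pre and post SDs. The tests and the other planned summaries are unaffected.

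**What to change.** In both places in Section 7.2, replace the reference to Cohen's d with the small-sample-corrected standardized mean change, and:
- name the denominator SD (SD of change, baseline SD or average pre/post SD);
- multiply by Hedges' correction J matched to the degrees of freedom of that denominator, for example 0.914 at n = 10 on 9 df, computed from the number of complete pairs in each analysis;
- report a 95% confidence interval beside the raw mean difference, which stays as planned.

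The choice of denominator can be left to the investigators. The baseline SD is not clearly best here, because entry requires PHQ-9 of 15 or more and selection on severity may narrow the baseline spread.

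The cost is one sentence and one multiplication per outcome. Reported standardized effects become about 9 to 11% smaller with a denominator on n − 1 df at n = 10 to 8, or about 4 to 6% smaller with the average SD at n = 10.

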### **3.3 Exploratory Study Endpoints**

The exploratory endpoint for this study will be to observe the changes in measures of depressive symptoms based on Montgomery-Asberg Depression Rating Scale (MADRS) and anhedonia based on Snaith-Hamilton Pleasure Scale (SHAPS); cognitive measures including Stroop Test, Revised Hopkins Verbal Learning Test (HVLT-R), and Digital Symbol Coding Test (DSCT). Response is defined by a 50% or more reduction in MADRS score.

An exploratory marker of response to tDCS is EEG peak alpha frequency (PAF) which will be measured pre- and post-tDCS. Another exploratory marker of response to tDCS is cerebral hemodynamic changes pre- and post-tDCS as measured by fNIRS using the NIRSIT system (OBELAB Inc.). Other exploratory predictors of treatment response include Adverse Childhood Experiences (ACE), premorbid intelligence quotient (pIQ), Wide Range Achievement Reading Test (WRART), and Socioeconomic Status (SES). These measures will only need to be administered once at the pre-treatment assessment.

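### Ordinary logistic regression of a 50% MADRS response on each baseline characteristic in 10 patients may give no finite odds ratio, and does so more often the stronger the predictor

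*Protocol*

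**What the plan says.** Protocol Section 7.1 sets the size: "Because this is a feasibility pilot study, formal power calculations are not needed. Target accrual is 10 subjects". Section 3.3 defines the binary outcome, "Response is defined by a 50% or more reduction in MADRS score", and Section 7.2 repeats it: "Treatment response will be defined as 50% or more improvement in MADRS score at post-treatment from pre-treatment".

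Section 7.2 plans the logistic regression twice. Under hypothesis 2.2.2b it is introduced as exploratory: "In the context of exploratory analysis, logistic regression will be used to assess associations between treatment response with each baseline characteristic". Under hypothesis 2.2.2c, which says that ACE, pIQ, WRART and SES "will be predictive of treatment response", the same method is repeated without that qualifier: "logistic regression will be used to assess associations between treatment response with each baseline characteristic". Hypothesis 2.2.2c is not among the objectives in Section 2.2. Section 3.3 lists the four measures as exploratory predictors.

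The section names no test (Wald, likelihood ratio or exact) and no penalised method, and gives no fallback for few responders or for separation. Missing data are handled by complete cases, so the number analysed can fall below 10. MADRS is scored before and after treatment, and its mean change is analysed by a paired test with raw and standardised differences. The change is not used as the outcome for the predictors.

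**The concern.** A logistic slope has no finite maximum-likelihood estimate in two situations: when every patient has the same outcome, and when all responders lie on one side of all non-responders on the predictor. With 10 patients neither is remote. The second becomes more likely as the true association strengthens, so the method tends to break down when hypothesis 2.2.2c is true.

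What is at stake is modest but real. The protocol describes itself as a pilot meant to generate hypotheses, so its product for these four measures is a set of effect estimates. An infinite odds ratio, or a finite one with a very wide interval, cannot be carried into the planning of a later study. A continuous outcome that avoids the problem is already being collected.

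**Working it through.** The protocol states no response rate, effect size or power for this analysis, so there is no figure to reproduce. **Inputs from the protocol:** n = 10; binary response; one model per characteristic; four characteristics. **Assumed:** response rates of 10–50%; a continuous, normally distributed predictor; correlation rho between the predictor and MADRS improvement of 0, 0.5 or 0.7.

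**1. Same outcome in all patients.** P(no responders) = (1−q)^10. For q = 0.1 this is 0.9^10 = 0.349; for q = 0.2, 0.8^10 = 0.107; for q = 0.3, 0.7^10 = 0.028.

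**2. No finite estimate when there is no association.** With k responders (1 to 9) and an unrelated continuous predictor, the chance of complete separation is 2/C(10,k), because only two of the C(10,k) orderings separate the groups. The total is therefore

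P(no estimate) = P(k=0) + P(k=10) + Σ P(k) × 2/C(10,k).

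For q = 0.2: 0.1074 + 0.2684×2/10 + 0.3020×2/45 + 0.2013×2/120 + 0.0881×2/210 + 0.0264×2/252 + … = 0.1074 + 0.0537 + 0.0134 + 0.0034 + 0.0008 + 0.0002 = 0.179. The same sum gives 0.436 at q = 0.1, 0.071 at 0.3, 0.030 at 0.4 and 0.020 at 0.5. Simulation agrees (44%, 18%, 7%, 3%, 2%).

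**3. No finite estimate when there is an association (simulation).**

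| Assumed response rate | rho = 0 | rho = 0.5 | rho = 0.7 |
|---|---|---|---|
| 20% | 18% | 27% | 39% |
| 30% | 7% | 14–15% | 26% |

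At 10% response the range is about 44% (rho = 0) to 63% (rho = 0.7). On another scale, an odds ratio of 4 per SD gives 34%, 20%, 16% and 15% at response rates of 20%, 30%, 40% and 50%. With four independent predictors and no association, at least one has no estimate in 34% of trials at 20% response and 17% at 30%.

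**4. Wald test.** For a binary predictor without empty cells, the largest |z| comes from the table 1/4 against 4/1: log OR = ln 16 = 2.773; SE = √(1 + 1/4 + 1/4 + 1) = 1.581; z = 1.75, p = 0.08. For a non-binary predictor, the largest |z| found by numerical search was 1.27, 1.66, 1.86, 1.961 and 1.992 with 1, 2, 3, 4 and 5 responders. The last corresponds to p = 0.046, for example with predictor values 1,4,4,4,4 in responders and 0,0,0,0,3 in non-responders. Across 120,000 simulated trials, with odds ratios up to 10 per SD, none passed 1.96.

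**5. Likelihood-ratio test.** Under separation the odds ratio is infinite but the statistic is defined. It equals −2[k ln(k/10) + (10−k) ln(1−k/10)], which is 6.50 for k = 1 (p = 0.011) and 10.0 for k = 2 (p = 0.0016). Counting separated datasets, rejection is about 29–30% at rho = 0.5 and 48–54% at rho = 0.7 for response rates of 20–40%. Type I error is about 9–12% instead of 5%.

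**6. The alternative.** A correlation with continuous MADRS change has an estimate whenever both variables vary. At n = 10 the critical |r| is 0.632, and Pearson power is 32% at rho = 0.5 and 68% at rho = 0.7. For an observed r of 0.5, the Fisher interval is tanh(0.549 ± 1.96/√7) = −0.19 to 0.86.

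**The case against.** The best defence is that this is an exploratory analysis in a feasibility pilot. The protocol disclaims power and multiplicity adjustment, and its primary questions are enrolment, completion and tolerability. The choice of test and the handling of separation could also be left to an analysis plan. This stands as a limit on importance. It does not remove the point: the protocol itself fixes the method, and the difficulty is whether an estimate exists, which a disclaimer of power does not address.

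Four stronger readings are tempting, and the documents do not support them.

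- A reader might infer that the analysis can never be significant. The protocol names no Wald test, a few contrived configurations with 4–6 responders do reach Wald p<0.05, and a likelihood-ratio test can reject.
- A reader might infer that a strong predictor would be reported as null. Perfect separation gives the largest likelihood-ratio statistic and would be obvious in a listing of 10 patients.
- A reader might infer that failure is frequent whatever happens. The protocol gives no response rate. With no association, failure is only 2–7% at response rates of 30–50%.
- A reader might infer that the continuous MADRS score is discarded. It is analysed for mean change and is only left unused as the outcome for the predictors.

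It is also fair to object that hypothesis 2.2.2c concerns response, so a correlation with MADRS change answers a neighbouring question. That stands, and is why responder status should be kept as a supplement.

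**Conclusion.** The point holds as a badly chosen method for an exploratory analysis. At an assumed 20% response, each predictor's odds ratio has no finite estimate in about 18% to 39% of trials as rho goes from 0 to 0.7; at 30% response the range is about 7% to 26%. These figures rest on the assumed response rates, a normal predictor and all 10 patients being analysable; fewer complete cases would raise them. Where a fit exists, the Wald test has practically no power, and the likelihood-ratio test rejects too often under no association.

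The case for the continuous outcome is estimability and error control more than power: at rho = 0.5 its 32% is little better than the likelihood-ratio test's inflated 29–30%. The change is worth making before analysis; the primary conclusions are unaffected either way.

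**What to change.** In Protocol Section 7.2, for hypothesis 2.2.2c and the matching sentence under 2.2.2b:

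- Make the main analysis the association of each baseline characteristic with the continuous MADRS change, by Spearman or Pearson correlation, or by regression of the post-treatment score adjusted for baseline MADRS. Report a 95% CI and a scatter plot for each.
- Report the 50% response rate descriptively with an exact CI.
- If an odds ratio for response is wanted, obtain it by Firth or exact logistic regression in place of ordinary maximum likelihood, and present it as a supplement.

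The cost is a few lines of text. No new data are needed, and Section 7.2 already uses correlation for PAF and baseline MADRS. There are two downsides to state openly: the continuous analysis addresses the amount of improvement and not the 50% response itself, and at n = 10 it supports estimation only.
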